## Abstract

**Background:**

Bipolar disorder (BD) is commonly associated with cognitive and functional impairments even during remission periods, and although a growing number of studies have demonstrated the benefits of psychotherapy as an add-on to pharmacological treatment, its effectiveness appears to be less compelling in severe presentations of the disorder. New interventions have attempted to improve cognitive functioning in BD patients, but results have been mixed.

**Methods:**

The study consists of a clinical trial comparing a new structured group intervention, called “Cognitive-Behavioral Rehabilitation,” with treatment as usual (TAU) for bipolar patients. The new approach is a combination of cognitive behavioral strategies and cognitive remediation exercises, consisting of 12 weekly group sessions of 90 min each. To be included in the study, patients must be diagnosed with BD type I or II, aged 18–55 years, in full or partial remission, and have an IQ of at least 80. A comprehensive neuropsychological battery, followed by mood, social functioning, and quality of life assessments will occur in three moments: pre and post intervention and 12 months later. The primary outcome of the study is to compare the time, in weeks, that the first full mood episode appears in patients who participated in either group of the study. Secondary outcome will include improvement in cognitive functions.

**Discussion:**

This is the first controlled trial assessing the validity and effectiveness of the new “Cognitive-Behavioral Rehabilitation” intervention in preventing new mood episodes and improving cognitive and functional impairments.

**Trial registration:**

Clinicaltrial.gov, NCT02766361. Registered on 2 May 2016.

**Electronic supplementary material:**

The online version of this article (doi:10.1186/s13063-017-1896-5) contains supplementary material, which is available to authorized users.

## Background

Bipolar disorder (BD) is a severe medical condition often associated with functional impairments even when affected individuals are euthymic [1]. Many studies report cognitive deficits in this population, most often in executive functions [2], attention [3], and verbal memory [4], which is coherent with recent meta-analyses on this topic [5, 6]. Recent studies have also established an association between cognitive deficits and functional impairments [7]. This evidence leads some authors to suggest that bipolar patients should benefit from cognitive rehabilitation strategies similar to those conducted in patients with schizophrenia [8].

Structured psychotherapies for BD associated with standard pharmacotherapy are associated with longer periods of remission, reduction in manic and depressive symptomatology, and faster recovery from episodes when compared to pharmacological treatment alone [9]. The majority of current studies suggest psychotherapy as an add-on to pharmacological treatment, even during euthymic periods [10].

Some studies have reported negative results regarding the effects of psychotherapies in preventing new mood episodes in BD [11]. A multicenter study including 253 patients with BD, in a heterogeneous sample with patients in diverse mood states, identified that Cognitive Behavior Therapy (CBT) prevented new mood episodes only in patients with less than 12 previous episodes [12]. Similar negative results in recovering and preventing mood episodes were found in group psychotherapy settings [13, 14]. The effectiveness of structured approaches most likely depends on the number of previous mood episodes [15]. Most negative studies included more severe presentations of BD, often including patients with more than two co-morbidities or many previous mood episodes; these observations have guided some researchers to delineate the importance of a staging model in BD [16].

Due to the disabling cognitive impairments in BD, new interventions were developed, namely cognitive rehabilitation and functional remediation. The first term describes a cognitive-oriented approach, developed to enhance specific cognitive domains such as attention and executive functioning [17]. The second one claims to enhance these same domains using an ecologic method in day-by-day tasks [18]. Despite such differences, we have chosen to use the term “cognitive remediation” to describe both approaches after considering the lack of evidence in this field. Deckersbach et al. [17] ran an open trial with 18 bipolar patients presenting depressive symptoms. After 14 individual sessions of cognitive remediation, patients demonstrated lower residual depressive symptoms and increased occupational and psychosocial functioning; the results persisted after three months. Another trial, conducted by Torrent et al. [19], evaluated cognitive remediation, delivering 21 weekly sessions in a group format. It consisted of three arms: (1) functional remediation; (2) psychoeducation; and (3) standard pharmacological treatment (TAU). The study included 239 euthymic, type I and type II bipolar patients, employing the Functioning Assessment Short Test (FAST) as the main outcome. Results suggest that psychoeducation and group cognitive remediation were better than TAU in improving functioning. Theory of mind [20] guided a new intervention designed to improve social cognition in BD [21]. The study included 37 patients randomly assigned to 18 group sessions of Social Cognition and Interaction Training (SCIT) or TAU alone. The SCIT group revealed an improvement in emotional perception and a decrease in depressive symptomatology. Lastly, Demant et al. [22] developed a 12-week group intervention of cognitive remediation. Their first trial included 46 BD patients, partially or fully remitted, randomly assigned to either cognitive remediation or standard treatment. The 26-week follow-up revealed no statistical differences in executive function, verbal memory, sustained attention, and psychosocial behavior, despite participants in the cognitive remediation group reporting a significant improvement in verbal fluency and quality of life [23].

These innovative trials encouraged the emerging field of cognitive remediation in BD. Cognitive remediation seems to be a feasible and partially efficacious method for treating residual depressive symptoms and improving functional recovery. Paradoxically, it is unclear whether such interventions are capable of promoting cognitive recovery in BD patients, the core reason for its creation.

Traditionally, cognitive remediation methodologies employ task-focused approaches. However, when testing its efficacy, restrictive settings are often utilized [24], which brings criticism for creating low ecological validity (i.e. the individual shows improvement in a specific task, but does not transfer it into their daily lives); consequently, new approaches are being proposed rather focusing on daily tasks [18].

Current psychological interventions for BD focus on the reduction of mood symptomatology and prevention of new bipolar episodes [25] and although these interventions may secondarily improve cognitive impairments, new psychological approaches enabling BD patients to deal with future episodes and addressing cognitive deficits are desirable.

This study aims to evaluate the effectiveness of a new intervention that combines cognitive rehabilitation and CBT strategies. Cognitive Behavioral Rehabilitation (CBR) was designed in an attempt to create a new intervention that could not only prevent new mood episodes (main outcome) but also improve memory, attention, executive functioning (secondary outcomes), and enhance quality of life (tertiary outcome).

### Hypotheses

The study hypothesizes that CBR, compared with TAU, will:Expand the period of time until the first new episode—our primary outcome measure;Improve attention, mental flexibility, working memory, and emotional recognition—our secondary outcome.

In an exploratory analysis, we will also assess whether CBR:Enhances functional, social skills, and quality of life scores;Increases sleep quality and knowledge about the disorder; andReduces impulsivity.

## Methods/Design

The study compares CBR with TAU, the latter being the commonly offered pharmacological treatment to bipolar patients. The psychological intervention will consist of 12 weekly group sessions, lasting 90 min each, and including eight to ten individuals. Participants will be randomly assigned to one of the two arms and followed for 12 months thereafter (Fig. 1). During the entire study, all patients will be medicated accordingly to their clinical needs and all changes in medication will be recorded, following the Necessary Clinical Adjustment (NCA) instrument. The NCA records medication adjustments implemented to reduce symptoms, improve response and functioning, or handle unbearable side effects [26].

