## Interventions

### Treatment as usual (TAU)

The control group from this study will receive standard outpatient treatment offered in our clinic, which involves psychopharmacological mood stabilization and regular contacts with mental health nurses. The type and dosage of pharmacological treatment will follow the physician decision, respecting individual demands. All pharmacological treatment will be monitored and recorded in accordance to the Litmus study [26].

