## Statistical analysis

### Sample size

The sample size calculation was based on the proportion of patients that remain episode-free after 12 months following a group intervention. Previous studies utilizing TAU exhibited a decrease of bipolar relapses in 30% of patients after a one-year follow-up [39]. The present study anticipates a 55% success rate in prevention of mood relapses, during the same period, in patients assigned to the CBR. Thus, considering an 80% power to obtain a 5% significance, an estimated sample of 28 individuals per group, 56 in total, should be sufficient to achieve significant results. A previous study conducted by the same research team [14] measured a drop-out rate of 10% in a one-year follow-up. For this latter reason, the study will consist of 60 participants.

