### Baseline and follow-up data

In order to measure the effectiveness of the intervention, the study will employ the following statistical tests: (1) Chi-squared and Mann–Whitney to test homogeneity between the groups at the beginning of the interventions; (2) Student’s t-test or Mann–Whitney to investigate the effects of such interventions, pre and post treatment, depending on the distribution of the data; (3) an analysis of variance, with and without adjustment for mood symptoms scores, IQ and BD duration, for comparison between groups; and (4) the Kaplan–Meyer survival method with log rank test for statistical analysis, to investigate the survival data between groups, which measures in weeks, the time to the first episode as an event. To be considered as an intervention completer, patients assigned to CBR should attend at least eight sessions (66.7%). Intent to treat analyses will be conducted in order to include all available data and missing data will be handled accordingly to the SPIRIT checklist recommendations (Additional file 1).

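### CBR patients are treated in three or four therapy groups, but the post-baseline tests treat all patients as independent; if outcomes correlate within groups, the type I error exceeds 5%

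*Protocol article*

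**What the plan says.** All of the following is in the protocol article.

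- **Delivery of CBR (Methods/Design):** "12 weekly group sessions, lasting 90 min each, and including eight to ten individuals".
- **Allocation (Methods/Design):** "Participants will be randomly assigned to one of the two arms". The unit is the patient. The ratio is not stated, but the sample size section gives equal arms.
- **Control arm (Treatment as usual):** "standard outpatient treatment offered in our clinic, which involves psychopharmacological mood stabilization and regular contacts with mental health nurses". No therapy groups are described, so only the CBR arm is nested.
- **Primary analysis (Baseline and follow-up data):** "the Kaplan–Meyer survival method with log rank test for statistical analysis, to investigate the survival data between groups".
- **Other between-arm comparisons (same section):** a t-test or Mann–Whitney test for pre/post effects, and "an analysis of variance, with and without adjustment for mood symptoms scores, IQ and BD duration, for comparison between groups". The covariates are all patient-level; therapy group is not among them.
- **Sample size:** 28 per arm, 56 in total, raised to 60 for drop-out, with no ICC and no design effect.

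The article does not mention clustering by therapy group anywhere, including under Limitations.

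**The concern.** Patients in one CBR group spend twelve sessions together. The Interventions section builds interaction into the treatment: group discussion, examples drawn from participants' own experience, and role-play. It is plausible that patients from the same group end up more alike than patients from different groups, while TAU patients have no such link. This is a partially nested design.

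A test that counts 30 CBR patients as 30 independent observations then uses too small a variance for that arm. The error goes one way: chance differences between a few therapy groups can be read as an effect of CBR. The primary endpoint and the cognitive outcomes are both exposed. Because the article names its tests, including the primary one, this concerns a stated choice and not a detail left open.

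**Working it through.** **1. Inputs from the article.** Group size m = 8 to 10; 60 patients, taken as 30 per arm. That gives 30/10 = 3 to 30/8 = 3.75 CBR groups, so three or four. Episode-free proportions at 12 months are 0.30 (TAU) and 0.55 (CBR). The 0.30 is a reading of "Previous studies utilizing TAU exhibited a decrease of bipolar relapses in 30% of patients after a one-year follow-up", which is ambiguous. Power is 80% and alpha 5%, taken as two-sided.

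**2. Input not in the article.** The ICC is assumed at 0.01, 0.05 and 0.10.

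**3. The plan's own figure.** The usual formula for two proportions gives

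n per arm = [1.96·√(2·0.425·0.575) + 0.842·√(0.30·0.70 + 0.55·0.45)]² / 0.25² = (1.370 + 0.569)² / 0.0625 ≈ 60.2, so 61.

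The stated 28 is not reproduced. One-sided testing needs 48. Only a one-sample formula against a fixed 30% gives 28 (27.7). This is a separate problem and the point here does not depend on it. What matters here is that 28 leaves no room for a design effect.

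**4. Effect of clustering on the standard error.** With clustering in the CBR arm only and equal arms:

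- design effect in the CBR arm: DE = 1 + (m − 1)·ICC
- variance of the difference is multiplied by (1 + DE)/2
- true type I error = 2·[1 − Φ(1.96 / √((1 + DE)/2))]

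For m = 10 and ICC 0.05: DE = 1.45; variance × 1.225; SE × 1.107; type I error = 2·[1 − Φ(1.771)] = 7.7%.

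| ICC (assumed) | DE, m = 8 / 10 | SE factor, m = 8 / 10 | True type I error, m = 8 / 10 | Unadjusted p needed to stay below 0.05, m = 8 / 10 |
|---|---|---|---|---|
| 0.01 | 1.07 / 1.09 | 1.02 / 1.02 | 5.4% / 5.5% | 0.046 / 0.045 |
| 0.05 | 1.35 / 1.45 | 1.08 / 1.11 | 7.1% / 7.7% | 0.034 / 0.030 |
| 0.10 | 1.70 / 1.90 | 1.16 / 1.20 | 9.2% / 10.4% | 0.023 / 0.018 |

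The last column is 2·[1 − Φ(1.96 × SE factor)].

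**5. Simulation of the planned tests.** There were 10,000 null trials per setting, 30 versus 30, with 30% episode-free at 12 months in both arms. The ICC is on a latent normal scale for the event times. The Monte Carlo standard error is about 0.2 to 0.3 percentage points.

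| ICC | Log-rank, 3 groups of 10 | Log-rank, 4 groups of 7–8 | t-test, 3 groups of 10 | t-test, 4 groups of 7–8 |
|---|---|---|---|---|
| 0 | 4.8% | 5.5% | 4.6% | 5.1% |
| 0.01 | 5.5% | 5.2% | 5.5% | 5.4% |
| 0.05 | 7.0% | 7.0% | 7.1% | 7.1% |
| 0.10 | 10.0% | 8.7% | 10.6% | 9.3% |

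The log-rank test follows the closed form about as closely as the t-test does.

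**6. Effect on size and power.** Putting DE on the CBR variance in the formula of step 3 gives 63, 71–75 and 82–88 per arm at ICC 0.01, 0.05 and 0.10, against 61 without clustering. Power at 30 per arm, with the clustering allowed for, is 48–49%, 42–44% and 37–39%, against 50% without clustering.

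**The case against.** The strongest reply is that the harm is conditional. The article reports no ICC and no evidence that outcomes cluster by therapy group. A reader might infer that the p-values are bound to be too optimistic; the documents do not support that. Near an ICC of 0.01 the inflation cannot be told from simulation noise. This stands, and it is why the point is stated as a range.

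Other stronger readings also fail:

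- **That every planned test is affected.** The chi-squared and Mann–Whitney tests of baseline homogeneity compare patients before any shared session, so therapy-group clustering does not reach them.
- **That planned confidence intervals are wrong.** The article names none. The point applies only to intervals that may later be reported from these analyses.
- **That patients in a group correlate because they share therapists.** The article mentions psychotherapists but not how many there are or who leads which group. Common therapists across groups at one site could even make the groups more alike.
- **That the primary endpoint is known to be hit hard.** Most of the follow-up lies after the sessions end, and all patients receive individually chosen medication. Expressed as a between-group SD on the log hazard, values of 0.2 / 0.3 / 0.4 with three groups of 10 give about 6.6% / 8.7% / 11.0% (40,000 null trials each). An SD of 0.1 gives 5.5%, close to the 5.1% found with no clustering. Nothing in the article says which applies.

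A further reply is that full correction is costly with so few groups. Analysing CBR group means with small-sample degrees of freedom cuts power from 80% to 68% even when the ICC is zero (three groups of 10). This also stands. It argues against resting the conclusion on a random effect or frailty estimated from three or four groups, but not against a sensitivity analysis.

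Finally, handling of clustering could sit in an analysis plan that is not shown. That carries limited weight, because the article already fixes the tests and lists the ANOVA covariates.

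**Conclusion.** The point holds in conditional form. Group delivery in one arm and tests that assume independent patients do not fit together, and nothing in the article compensates. If outcomes correlate within CBR groups, the nominal 5% two-sided type I error becomes about 5.4–5.5%, 7–8% or 9–10% at ICCs of 0.01, 0.05 or 0.10. This covers the post-baseline between-arm comparisons, including the primary log-rank test. In practice, an unadjusted p-value between about 0.02 and 0.05 is the zone where the conclusion could depend on the ICC.

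The result rests on equal arms of 30, groups of 8 to 10, two-sided testing and an assumed ICC. The Mann–Whitney test was not simulated; it makes the same independence assumption. The point is a cheap improvement, not a flaw that invalidates the trial.

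**What to change.** 1. Record the CBR group number for each patient.
2. Keep the log-rank test as the primary test.
3. For the primary and secondary between-arm comparisons, also report the p-value and interval with the CBR-arm variance multiplied by 1 + (m − 1)·ICC at fixed ICCs of 0.01, 0.05 and 0.10, with m the mean size of the CBR groups formed. For the primary endpoint this can be done approximately on the log hazard ratio, whose variance is about 1/(CBR events) + 1/(TAU events), by inflating the first term.
4. For continuous outcomes, add as supportive analysis a partially nested mixed model with a random group effect in the CBR arm only and small-sample degrees of freedom.
5. State in advance that a CBR effect is called robust only if it survives step 3.

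The cost is one variable, which the team already knows, and a few sentences in the analysis plan. No treatment procedure changes. The Trial status section reports 40 patients included and 11 in follow-up, so at that stage the change could be fixed before results were known. The downside is wider intervals, some loss of power for the robust claim, and an ICC that three or four groups cannot estimate well. That is why the ICCs in step 3 are fixed and not estimated.

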### Participants

In order to be included, patients must be aged 18–55 years, literate, present an IQ score higher than 80, have been diagnosed with bipolar I or II based on Structured Interview for DMS IV (SCID) [27], and be in full or partial remission according to the DSM IV [28]. Exclusion criteria are: presence of substance or alcohol abuse in the last six months; current suicide risk; organic mental disorders; or scores higher than 12 in the Montgomery-Åsberg Depression Rating Scale (MADRS) or the Young Mania Rating Scale (YMRS) at the beginning of the intervention [28].

Recruiting will take place at an outpatient service provided by the Bipolar Disorder Research Program (PROMAN) at the University of São Paulo Medical School, Brazil. Patients will receive invitations individually and sign an informed consent. This research was approved by an internal ethical committee and registered in ClinicalTrials.gov: NCT02766361.

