### Procedure and outcomes

Once included, patients will complete the Portuguese versions of the following self-report questionnaires:Abbreviated instrument of quality of life (WHOQOL-bref) [29]: evaluating quality of life scored in four domains: physical, psychological social, and environmentalBarratt Impulsiveness Scale 11 (BIS 11) [30]: assessing the personality/behavioral construct of impulsiveness. It includes 30 items describing common impulsive or non-impulsive behaviors and preferencesSocial Skills Inventory (IHS) [31]: self-report instrument assessing social skills. It consists of 38 items, each describing a situation of interpersonal relationship and a demand for ability to react to that situationBiological Rhythms Interview of Assessment in Neuropsychiatry (BRIAN) [32]: consisting of 21 items divided into five main areas related to circadian rhythm disturbances in psychiatric patients, including sleep, activities, social rhythms, eating patterns, and predominant rhythmFunctioning Assessment Short Test (FAST) [33]: a 24-item interview assessing functional impairments in BD, and including autonomy, occupational functioning, cognitive, financial issues, interpersonal relationships, and leisure timeKnowledge about Affective Disorders Interview (KADI): brief questionnaire evaluating the patient’s knowledge about prognostic, medication, etiology, symptoms, and diagnosis of BD [34]

A brief neuropsychological battery will be conducted, which includes two subtests of matrix reasoning and vocabulary from the Wechsler Abbreviated Scale of Intelligence (WASI) [35] and following subtests from the Cambridge Neuropsychological Test Automated Battery (CANTAB): Motor Screening Task (MOT); Rapid Visual Information Processing (RVP); Reaction Time (RTI); Spatial Span (SSP); Spatial Working Memory (SWM); One Touch Stockings of Cambridge (OTS); Pattern Recognition Memory (PRM); Delayed Matching to Sample (DMS); Attention Switching Task (AST); and Emotion Recognition Task (ERT).

Participants will also complete the initial assessment and mood module of the Structured Clinical Interview for DSM-IV (SCID-IV) [36] at week 12 after inclusion into the study and 12 months thereafter.

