## Trial status

The study is underway and currently includes 40 patients, of which 29 have completed the initial evaluations and 11 are currently in the follow-up period following participation in either CBR meetings or TAU.

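### Follow-up runs 12 months from random assignment in one section but 12 months from the end of the intervention in others, and the primary time-to-episode endpoint has no stated time zero

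*Protocol article*

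**What the plan says.** All references are to the protocol article.

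- **Methods/Design** ties follow-up to assignment: "Participants will be randomly assigned to one of the two arms and followed for 12 months thereafter".
- **Abstract, Methods** ties the last assessment to the intervention: the assessments "will occur in three moments: pre and post intervention and 12 months later".
- **Procedure and outcomes** schedules the SCID mood module "at week 12 after inclusion into the study and 12 months thereafter".
- **Sample size** plans on "the proportion of patients that remain episode-free after 12 months following a group intervention".
- **Trial status** says that "11 are currently in the follow-up period following participation in either CBR meetings or TAU", so follow-up is again something that comes after treatment.

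The primary outcome in the abstract is to "compare the time, in weeks, that the first full mood episode appears in patients who participated in either group". The Hypotheses section and the Baseline and follow-up data section also define it as time to first episode, analysed by Kaplan-Meier and log-rank. None of the three gives a starting point. The Baseline and follow-up data section commits to intention-to-treat analyses.

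**The concern.** A time-to-event endpoint needs an origin, an end and a rule for which events count. The article gives two end points for follow-up, about 12 weeks apart, and no origin. Those 12 weeks are the length of the treatment phase, so the discrepancy decides whether treatment-phase episodes belong to the primary analysis.

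If the clock starts after the intervention, a patient who relapsed in week 6 has already had a first episode. Either the patient is removed, or a later episode is recorded as the first. Removal restricts the comparison to patients who stayed well for 12 weeks after randomisation. CBR is meant to influence that outcome, so the two groups entering the analysis are no longer the randomised groups. With the origin left open, it could also be chosen after the data are seen.

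**Working it through.** **Follow-up windows, side by side**

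| Section | Anchor | End, in weeks |
|---|---|---|
| Methods/Design | random assignment | about 52 |
| Procedure and outcomes (SCID) | week 12 after inclusion, plus 12 months | 12 + 52 = about 64 |
| Abstract, Methods | post-intervention visit, plus 12 months | about 64, if treatment takes 12 weeks |
| Sample size; Trial status | after the intervention | in line with about 64 |

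Inclusion and randomisation are taken as the same day, because the article gives no gap between them.

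**The plan's own figure.** The Sample size section gives 28 per group for 30% against 55%, with 80% power and 5% significance. The two-sided two-proportion formula gives

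n = [1.96·√(2 × 0.425 × 0.575) + 0.842·√(0.30 × 0.70 + 0.55 × 0.45)]² / 0.25² = (1.370 + 0.569)² / 0.0625 ≈ 60.2, so 61 per arm.

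The stated 28 is not reproduced. That is a separate fault and does not depend on the clock. Only the 30% and 55% rates are used below.

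**Inputs for the clock comparison.** Episode-free at one year: 30% TAU and 55% CBR (Sample size; the TAU wording is ambiguous and is read as 30% episode-free). 60 participants, taken as 30 per arm. Assumptions: constant hazards, the full CBR effect from randomisation, no dropout, two-sided 5%.

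- S(t) = S(52)^(t/52), and the hazard ratio is ln 0.55 / ln 0.30 = 0.497, so |ln HR| = 0.700.
- Week 12: TAU 0.30^(12/52) = 0.757; CBR 0.55^(12/52) = 0.871.
- Week 64: TAU 0.30^(64/52) = 0.227; CBR 0.55^(64/52) = 0.479.
- First episodes in weeks 0 to 12: 30 × 0.243 + 30 × 0.129 = 7.3 + 3.9 = 11.1.
- Still at risk at week 12: 30 × 0.757 = 22.7 TAU; 30 × 0.871 = 26.1 CBR.

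Power = Φ(0.700 × √d / 2 − 1.96), where d is the expected number of events.

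| Clock | Expected events d | Power |
|---|---|---|
| Randomisation to week 52 | 30 × 0.70 + 30 × 0.45 = 34.5 | Φ(2.056 − 1.96) = 54% |
| Randomisation to week 64 | 30 × 0.773 + 30 × 0.521 = 38.8 | Φ(2.181 − 1.96) = 59% |
| Week 12 to 64, early relapsers dropped | 22.7 × 0.70 + 26.1 × 0.45 = 27.7 | Φ(1.841 − 1.96) = 45% |
| Week 12 to 52, early relapsers dropped | 22.7 × (1 − 0.30^(40/52)) + 26.1 × (1 − 0.55^(40/52)) = 23.4 | Φ(1.692 − 1.96) = 39% |

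**Sensitivity: no CBR effect until week 12.** Early first episodes rise to 60 × 0.243 = 14.6, and 22.7 remain at risk in each arm. Events in weeks 12 to 64 are 22.7 × (0.70 + 0.45) = 26.1. The week 12 to 64 clock then has power Φ(0.700 × √26.1 / 2 − 1.96) = 43%. The randomisation clock to week 64 carries 14.6 uninformative events and has power Φ(26.1 × 0.700 / (2 × √40.7) − 1.96) = Φ(1.434 − 1.96) = 30%. The power ranking therefore depends on how early CBR acts.

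**The case against.** The strongest reply is that no section gives the primary clock two values. Methods/Design sets a follow-up period, Procedure and outcomes sets SCID visits, and Sample size sets a planning proportion. An unstated time zero in a condensed article may be settled in the full protocol or the SAP. The word for what follows assignment may be loose, since it comes just after the sentence on the 12 sessions. Fig. 1, the schedule, is not shown. Part of this stands: time zero is undefined rather than contradicted, and the treatment of early episodes is left open. It does not remove the finding, because the 52-week and 64-week windows are both printed and cannot both hold.

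Three stronger readings are tempting, and the document does not support them.

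- **That the plan breaks intention to treat.** No section says that the clock starts after treatment or that early relapsers are dropped. The conflict arises only if that reading is adopted.
- **That the mood-score exclusion removes early relapsers from CBR alone.** The criterion is "scores higher than 12 in the Montgomery-Åsberg Depression Rating Scale (MADRS) or the Young Mania Rating Scale (YMRS) at the beginning of the intervention". It is listed among the exclusion criteria for all patients, and nothing says that it is applied after randomisation or in one arm. TAU is itself described under the Interventions heading, and the Trial status section treats it as something patients take part in. Figures based on a wait between randomisation and session 1 would rest on a delay that the article does not give.
- **That the whole post-treatment assessment is fixed at week 12.** The week number belongs to the SCID only. The abstract ties the other assessments to the intervention without a week.

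The sensitivity result also carries weight: if CBR acts only once delivered, counting the treatment weeks costs power.

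**Conclusion.** The concern holds in this form: the length of follow-up is contradictory by about 12 weeks (52 against 64), and the primary endpoint has no stated origin and no rule for treatment-phase episodes. Under the constant-hazard assumptions, about 11 of about 39 first episodes expected by week 64 depend on that rule. Power is about 45% for a week 12 to 64 clock that drops those patients, against 54% or 59% from randomisation. Between the window as printed in Methods/Design and the post-intervention clock, the gap is about 9 points; the 14-point gap applies only if the randomisation clock is extended to week 64.

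These figures illustrate the stakes and are not forecasts. They measure lost information; the direction of any selection bias cannot be derived from the document. The case for randomisation as time zero rests on keeping the randomised comparison intact and on agreement with the stated intention-to-treat analysis, not on power, whose ranking reverses if CBR has no early effect. Because this is the primary endpoint, it should be settled before the primary analysis.

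**What to change.** - Define time zero as the date of randomisation in both arms.
- Count every first full mood episode from that date, including those in the 12 treatment weeks, and keep every randomised patient.
- Set one administrative censoring date: the last scheduled SCID, about week 64.
- Report the 52-week Kaplan-Meier proportion in each arm, to match the one-year rates in the Sample size section.
- Reword the abstract, Methods/Design, Procedure and outcomes and Sample size sections to this single anchor.

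The cost is small: rewording and use of each patient's randomisation date, with no added visit, since SCIDs at week 12 and about week 64 are already scheduled. The price is that episodes occurring before CBR has been fully delivered count in the comparison, which dilutes the estimate if CBR acts late. The Trial status section reports 40 of the planned 60 patients included, so the wording can still be settled before the primary analysis.
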